### Objectives

This proposed study aims to evaluate the effectiveness of an app-based intervention developed based on relevant scientific theories (e.g., Theory of Planned Behavior, the Haddon Matrix, and the Mobile Learning framework) to prevent unintentional injury incidence among preschoolers through changing parental behavior. We also sought to improve safety-related knowledge, attitudes, and behaviors of the caregivers.

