### Interventions for control and intervention groups

We will provide the participants in both experimental groups with an app-based parenting education program that targets training on pediatric diseases and parenting skills but excludes information about unintentional injury prevention. The education program will use short essays, games, cartoons and videos to disseminate knowledge and skills about optimal parenting of young children. The content, interaction, survey and feedback, and personal module of app will be identical for both groups.

The intervention group’s app will have additional components that are focused on unintentional injury prevention. As detailed below, the intervention group’s app will have features geared particularly toward parenting and education on child injury prevention, including some features that rotate seasonally (e.g., drowning prevention in summer).

Both parenting and injury prevention features in the app will be available throughout the intervention time period so that the users can retrieve any information they want on a repeated basis.

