### Data collection

Data will be collected at three time points: baseline, 3 months post-intervention, and 6 months post-intervention. All data will be collected through app-based online surveys and will be stored in the backend database of app with password limiting the access. If caregivers fail to complete app-based surveys, we will provide printed paper questionnaires to participants through the support of facilitating teachers. In addition, an independent app-based survey among a sample of 100 caregivers will be conducted at each time period to test the reproducibility of collected data.

We also will collect compliance data through electronic strategies embedded in the app. These will include frequency of login, length of time using the app at each log-in, the number of knowledge disseminations used and listed as bookmarks, the number of published comments, and so on.

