### Data analysis plan

Analysis will follow the intention-to-treat approach [38]. Descriptive data (mean, standard deviation, median, inter-quartile range, proportion) will be calculated to describe the characteristics of primary and secondary outcome measures and covariates. Chi-square test (categorical outcomes) and two sample independent *t*-test (continuous outcomes) will examine differences in unintentional injury incidence and other outcome indicators between the two arms at each time point (baseline, 3 months, 6 months). Chi-square test (categorical outcomes) and analysis of variance for repeated measurement data (continuous outcomes) will detect differences across the three time points for each arm.

The primary analysis will be conducted through Generalized Estimation Equation (GEE) models, which will test the effectiveness of the app-based intervention based on the interaction of group (intervention vs. control) with time (baseline, 3 months, 6 months) after adjusting for socio-demographic variables (age, sex, household income) and compliance to the intervention (use of the app-based interventions).

Missing values will be imputed using the Expectation Maximization algorithm (EM). To test the robustness of results, sensitivity analysis will be conducted by comparing primary and secondary outcome data collected through the online app-based survey and those completed using a printed questionnaire survey. Statistical analysis will be performed through Stata/IC 12.1. Statistical significance will be based on 2-sided tests at the level of 0.05.

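### The primary GEE adjusts for app use recorded after randomisation; if use differs by arm and enters by period, the group-by-time effect can be biased in either direction

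*Protocol article*

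**What the plan says.** All references are to the protocol article.

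- **Principle.** The Data analysis plan opens with "Analysis will follow the intention-to-treat approach".
- **Primary model.** The same section says "The primary analysis will be conducted through Generalized Estimation Equation (GEE) models". The effect is tested "based on the interaction of group (intervention vs. control) with time (baseline, 3 months, 6 months", and the model is fitted "after adjusting for socio-demographic variables (age, sex, household income) and compliance to the intervention (use of the app-based interventions". No primary model without compliance is described.
- **What compliance is.** Data collection says "We also will collect compliance data through electronic strategies embedded in the app", and then "These will include frequency of login, length of time using the app at each log-in, the number of knowledge disseminations used and listed as bookmarks", with published comments also counted.
- **Difference between the arms.** Both arms receive an app, but under Interventions for control and intervention groups, "The intervention group’s app will have additional components that are focused on unintentional injury prevention". Intervention design adds an injury forum topic each week for the intervention arm only, and a monthly expert consultation on injury prevention for that arm.
- **Route to the effect.** The Objectives say the app is meant "to prevent unintentional injury incidence among preschoolers through changing parental behavior".
- **Other comparisons.** Chi-square tests compare the arms on the primary outcome at each time point without covariates. They are described apart from the analysis named as primary.

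**The concern.** Three features make app use unsuitable as a covariate in a primary intention-to-treat model. It is recorded after allocation. Allocation can change it, because one arm has more to read, discuss and log in for. It is also the step through which a caregiver can benefit at all.

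Conditioning on such a variable can do two things. It can remove part of the effect under test, because the arms are compared at equal use when unequal use may be part of what assignment does. It can also bring in a non-randomised comparison: caregiver traits such as diligence may drive both app use and the child's injury risk, and holding use constant then unbalances those traits between the arms.

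What is at stake is the trial's main conclusion. A real benefit could be weakened, lost or exaggerated, and an app with no effect could appear harmful or protective.

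**Working it through.** **Inputs from the document.** Control incidence over three months is 23% and the effect size is 0.75 (Sample size), read here as a risk ratio. The intervention risk is then 0.23 × 0.75 = 0.1725. The corresponding odds ratio is (0.1725/0.8275) / (0.23/0.77) = 0.2085/0.2987 = 0.70. The plan gives no figure for app use, so there is none to reproduce.

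**Assumed inputs.** Let u be a standard normal caregiver trait.

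- Use per period is Poisson with mean m × exp(0.4u − 0.08), where m = 3 in control and 6 in intervention (100% higher).
- Injury risk is 0.23 × exp(−bu − b²/2).
- At follow-up in the intervention arm, risk is multiplied by 0.75^(use/6) when the benefit acts wholly through use.
- With b = 0.3 heavier users have lower risk; with b = −0.3 they have higher risk; with b = 0 there is no link.

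**Models.** Logistic group × time, fitted (i) without use, (ii) with one fixed use value per caregiver, and (iii) with use by period, zero at baseline. There were 300,000 simulated caregivers per arm. Point estimates equal those of a GEE with independence working correlation.

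**Group × time odds ratios at 3 / 6 months:**

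| Scenario | No use term | Fixed use | Use by period |
|---|---|---|---|
| Benefit via use, b = 0.3 | 0.74 / 0.73 | 0.74 / 0.73 | 1.03 / 1.03 |
| Benefit via use, b = 0 | 0.71 / 0.71 | 0.71 / 0.71 | 0.79 / 0.79 |
| Benefit via use, b = −0.3 | 0.67 / 0.69 | 0.67 / 0.69 | 0.59 / 0.60 |
| No effect, b = 0.3 | 1.01 / 1.01 | 1.01 / 1.01 | 1.28 / 1.29 |
| No effect, b = −0.3 | 1.00 / 1.00 | 1.00 / 1.00 | 0.77 / 0.77 |
| Equal use (mean 3 in both arms), benefit via use, b = 0.3 | 0.86 / 0.85 | 0.86 / 0.85 | 0.86 / 0.85 |

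In the first scenario, a contrast of the arms at follow-up only moves from 0.73 to 1.03 once use is added.

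**Why the coding matters.** A fixed value shifts a caregiver's baseline and follow-up log odds by the same amount, so it nearly cancels from the interaction. Use by period is zero for everyone at baseline, so it competes directly with the interaction. Approximately, adjusted log OR = unadjusted log OR − (use coefficient) × (arm difference in mean use). In the first row, ln(1.032/0.740) = 0.33. With a difference of 3 items, that is a coefficient of about −0.11 per item. If the arm difference is zero, the shift is zero, as the last row shows.

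**Smaller arm differences.** With period-specific total use 20-100% higher in the intervention arm, over a range of trait strengths, a true interaction odds ratio of about 0.68-0.76 becomes 0.62-0.99, and a null becomes 0.80-1.21. In a separate check with a true odds ratio of 0.70 acting wholly through injury content, adjusting for total use gave 0.70 with equal use, 0.72-0.77 with use 20% higher, and 0.75-0.93 with use 50% higher. The table uses doubled use and a particular trait strength, so some of its entries fall slightly outside the first range. The limits depend on what is assumed.

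**The case against.** The strongest defence is that the tested term is group by time and the article does not say how compliance is coded. With one fixed value per caregiver the interaction is practically unchanged, and the same holds if use is equal in both arms. The incentives, teacher reminders and inactivity alert are not arm-specific, so a difference in use is plausible but not established. The unadjusted chi-square comparisons also guarantee that a contrast free of compliance will be reported.

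All of this stands, and it limits the point to a conditional one. It does not rescue the wording. Use is logged throughout and the model is longitudinal, so coding by period is a natural implementation. In the harmless codings the term contributes nothing to the test. An unseen analysis plan could settle the coding, but the article has already fixed the term's presence. The chi-square comparisons lessen the harm without curing it, because they are not primary.

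A reader might infer more: that the primary estimate certainly ceases to be the intention-to-treat effect, or that a working app will be made to look harmful. The documents do not support either. A shift such as 0.70 to 1.12 can be produced, but only by adjusting for use of injury content, which is zero in controls. Data collection lists general measures that exist in both arms. In that near-worst case the assumed strength of the link with diligence alone moved the result from 1.03 to 1.81, so no single figure is usable. A reader who expects only lost benefit or false harm would also be mistaken: if heavier users are at higher risk, the bias favours the app.

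**Conclusion.** Wrong as written. The Data analysis plan promises intention-to-treat and then puts a post-randomisation variable on the causal route into its only named primary model.

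The harm arises if use differs by arm and enters by period. In that case, with total use 20-100% higher in the intervention arm, a true interaction odds ratio of about 0.7 becomes about 0.6-1.0, and a null becomes about 0.8-1.2. Clear reversal above 1 needs strong assumptions: a covariate that is zero in controls, or a strong link between use and diligence.

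The presence of the flaw is certain from the text. Its size and direction are not, because use by arm, the link between use and risk, and the coding of the covariate are all assumed here.

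**What to change.** - **Primary model.** Delete the compliance term from the primary GEE and adjust only for the baseline covariates already listed: age, sex and household income.
- **App use.** Report it only in a separate analysis labelled as secondary. State there that a dose-response analysis remains confounded by caregiver traits. A complier-average analysis is possible only if the logs separate injury content from parenting content, because controls also use an app; Data collection does not say that they do.

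The first change costs one clause and needs no new data. The complier-average option should be promised only after the content of the logs has been confirmed.

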****Method**:**

A single-blinded, 6-month, parallel-group cluster randomized controlled trial with 1:1 allocation ratio will be conducted in Changsha, China. In total, 2626 caregivers of preschoolers ages 3–6 years old who own a smartphone will be recruited from 20 preschools. Clusters will be randomized at the preschool level and allocated to either the control group (routine education plus app-based parenting education excluding unintentional injury prevention) or the intervention group (routine education plus app-based parenting education including unintentional injury prevention). The app-based injury prevention program was developed based on the Theory of Planned Behavior, the Haddon Matrix, the Mobile Learning framework, and a needs assessment. Data collection will be conducted at baseline, 3-month, and 6-month follow-up via app-based survey plus printed questionnaire survey. The primary outcome measure is unintentional injury incidence among preschoolers in the past 3 months. Secondary outcome measures include economic losses due to unintentional injury in the past 3 months, the Incremental Cost-Effectiveness Ratios (ICERs), and parent’s attitudes and behaviors concerning supervision to prevent preschooler unintentional injury in the past week. An intention-to-treat approach will be used to evaluate outcome measures. Chi-square tests will examine differences for outcome measures between groups at each time point and generalized estimation equations (GEE) will test the overall effectiveness of the app-based intervention. Missing outcome data will be imputed using the Expectation Maximization algorithm (EM).

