### Sample size

Sample size was calculated based on our primary hypothesis, to detect a difference between the intervention and control groups in unintentional injury incidence among preschoolers in the prior 3 months. Previous studies reported an unintentional injury incidence of 25.5% among preschoolers in central China in the past 1 year [22] and an effect size of 0.64 between intervention and control groups [23]. Considering 1 year recall periods underestimate injury rates by 55 and 72% (most are minor injuries) compared with one-month recall periods [24, 25], and use of a strict operational definition that restricts injury events to those that cause activity restriction of 1 day or longer or are treated by a doctor or other medical professional substantially undercounts injury events (typically minor or moderate injuries) [26], we assume unintentional injury incidence among preschoolers in the past 3 months will be 23%. On the basis of a previous report [27], we estimate an intra-class correlation (ICC) of 0.005 within a preschool of 140 students. Predicting an incidence of 23% in the control group, an effect size of 0.75 between intervention and control groups, and an ICC of 0.005, α = 0.05, 1-ß = 0.80, a minimum sample size of 1181 caregivers is needed for each group. Conservatively estimating an attrition rate of 10% in the six-month follow-up study, we will require a recruited sample size of 1323 each group. In total, therefore, we will enroll 2626 participants. Since most preschools have far more than 100 students enrolled, 20 preschools are amply sufficient to recruit the needed sample size.

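### Missing injury outcomes are to be filled by EM with no allowance for imputation uncertainty, so standard errors come out modestly too small, and the stated sensitivity analysis does not test the assumption about non-responders.

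*Protocol article*

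**What the plan says.** Protocol article, Data analysis plan: "Missing values will be imputed using the Expectation Maximization algorithm (EM". The Abstract (Method) makes clear that outcomes are included: "Missing outcome data will be imputed using the Expectation Maximization algorithm (EM".

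Neither place mentions several imputed data sets, a pooling rule or a corrected variance. The one bootstrap in the article, under Secondary outcome measures, is for the cost-effectiveness ratios only.

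The outcome data feed chi-square tests at each time point and the main model: "The primary analysis will be conducted through Generalized Estimation Equation (GEE) models". The effect is tested there as a group-by-time interaction over baseline, 3 and 6 months. "Statistical significance will be based on 2-sided tests at the level of 0.05".

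For robustness, the plan offers one check: "sensitivity analysis will be conducted by comparing primary and secondary outcome data collected through the online app-based survey and those completed using a printed questionnaire". Under Data collection, paper goes to caregivers who fail to complete the app survey.

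**The concern.** EM gives parameter estimates and, from them, an expected value for each missing item. A data set completed in this way has no residual scatter in the filled cells, and the analysis counts every filled cell as a full observation. The standard error shrinks for both reasons, so intervals are too narrow and the 5% test rejects too often.

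The primary outcome is whether a child was injured in the prior three months. Its expected value is a fraction such as 0.23. A chi-square test on counts cannot take fractions, so someone will have to decide, outside the plan, what to do with them. Rounding would turn almost every missing child into an uninjured one.

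The plan's robustness check would not reveal either problem, because everyone in it has supplied an outcome.

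**Working it through.** **Inputs from the article.** Control incidence 23%, effect size 0.75 and ICC 0.005 (Sample size: "Predicting an incidence of 23% in the control group, an effect size of 0.75 between intervention and control groups, and an ICC of 0.005"); attrition 10% (Sample size); 10 preschools per arm (School recruitment); two-sided 5% level. As a check on the 10%: 1181 / 0.9 = 1312.2, rounded up to 1313 per group, and 2 × 1313 = 2626, the stated total. The printed 1323 per group does not fit that total (2 × 1323 = 2646), but nothing below depends on it.

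**Assumptions not in the article.** Outcomes missing completely at random; baseline complete, since the baseline survey follows straight after consent; one follow-up time; within-child correlation r between surveys of 0 or 0.3; equal variance at both surveys.

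**Step 1: a contrast at follow-up only.** Let f be the missing fraction and work per child in units of the outcome variance.
- True variance of an arm mean: 1/(1−f).
- Variance reported after a mean fill: 1−f.
- Reported/true SE = 1−f. Size = 2 × [1 − Φ(1.96 × (1−f))].
- f = 0.10: SE ratio 0.90, size 7.8%.

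**Step 2: the planned contrast, change from baseline by arm.** The fill uses arm and baseline.
- True variance: (1−r²)/(1−f) + (1−r)².
- Reported variance: (1−f)(1−r²) + (1−r)².

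| f | r | True | Reported | SE ratio | Size |
|---|---|---|---|---|---|
| 0.10 | 0 | 2.111 | 1.900 | √0.900 = 0.949 | 6.3% |
| 0.10 | 0.3 | 1.501 | 1.309 | √0.872 = 0.934 | 6.7% |
| 0.20 (hypothetical) | 0 | 2.250 | 1.800 | √0.800 = 0.894 | 8.0% |
| 0.20 (hypothetical) | 0.3 | 1.628 | 1.218 | √0.748 = 0.865 | 9.0% |

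The baseline part of the contrast is unaffected by the fill, so the loss of size is smaller than in Step 1.

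**Step 3: simulation under the null.** These runs used 10 preschools per arm and about 131 children in each (2626/20), with a cluster-level t test standing in for the GEE.
- Change-from-baseline contrast, 10% missing: size about 6.1 to 6.5%.
- Follow-up-only contrast, 10% missing, fill by arm and baseline status, 4000 replicates: 7.9% with ICC 0 and 6.4% with ICC 0.005.
- Follow-up-only contrast, 10% missing, ICC 0.005, fill by arm mean, 20,000 replicates: 7.5%.
- Multiple imputation (10 sets, Rubin's rules), follow-up-only contrast, 10% and 20% missing: 4.6 to 5.4%.

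**Step 4: rounding (hypothetical).** Suppose every filled value below one half becomes zero.
- Equal 10% loss: both arms fall from 23% to 0.23 × 0.90 = 20.7%, and the null ratio stays at 1.
- Loss of 15% in the intervention arm and 5% in control: (0.23 × 0.85)/(0.23 × 0.95) = 0.1955/0.2185 = 0.89 under a true null. With the losses the other way round it is 0.2185/0.1955 = 1.12.

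**Step 5: the sensitivity analysis.** The comparison is of "comparing primary and secondary outcome data collected through the online app-based survey and those completed using a printed questionnaire survey". One group answered promptly in the app; the other answered on paper after failing to do so. Survey mode and willingness to respond are mixed together, and no child without an outcome appears in either group.

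**The case against.** **EM may not mean a single fill.** The article says only that values are imputed using EM. If the full plan uses EM for likelihood estimation, or to start multiple imputation, the standard-error point falls away. That possibility stands, but the text does not say so, and one completed data set is the plain reading of it.

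**The size is easily overstated.** A reader might take 7.8% as the type I error of the primary test. That figure belongs to a follow-up-only contrast, whereas the article tests group by time with baseline included. Losses of 20% or 30% are likewise not the plan's: it gives 10%, calls that conservative, and adds reminders and a paper fallback. This objection stands.

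**A false treatment effect is not shown.** A reader might infer that the method manufactures a benefit. That needs both rounding and unequal loss between arms, and the article states neither. Without rounding, a fill of this kind leaves the contrast unbiased when outcomes are missing completely at random; the harm is to the standard error.

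**The online-v-paper comparison has some value.** Paper respondents are reluctant responders, so a difference between them and app responders hints at whether non-responders differ too. The article presents it as a robustness check, not as a missing-data analysis, and a further sensitivity analysis is something an unseen analysis plan could hold. It would therefore be wrong to call the comparison empty or to fault the article for omitting another. What remains is that this check cannot test the assumption about people who never answered.

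**Conclusion.** The point holds, at modest size. As written, the plan fixes an imputation method that carries no imputation uncertainty into the primary test and produces fractions for a binary outcome. At the planned 10% attrition the group-by-time test has a type I error of about 6.1 to 6.7% instead of 5%, so a nominal 95% interval covers about 93.3 to 93.9%. A follow-up-only contrast, such as the tests at each time point, would run at about 7 to 8%. At a hypothetical 20% loss the group-by-time figure is about 7 to 9%.

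These figures rest on the single-fill reading, outcomes missing completely at random, complete baseline data, the two values assumed for within-child correlation, and a simple contrast standing in for the GEE. The direction is secure; the exact size is not. The ratio of 0.89 in Step 4 illustrates what rounding with unequal loss could do and is not a prediction for this trial.

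The change should be made before analysis. The point does not call the trial design into question.

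**What to change.** In the Data analysis plan and the Abstract, replace single EM imputation with multiple imputation of the binary injury outcome:
- a logistic imputation model with preschool as a random effect, or another approach that respects clustering. Fixed preschool terms would be collinear with arm and public/private status, both of which are constant within a preschool;
- predictors: arm, public/private, baseline and 3-month injury, age, sex, household income and app use;
- at least 20 imputed sets, each analysed with the planned GEE and pooled by Rubin's rules.

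If EM was meant only for likelihood estimation or as a starting step for multiple imputation, say so and state how the standard errors are obtained.

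Keep the online-v-paper comparison, labelled as a description of survey mode. Add a re-run of the primary contrast in which the imputed injury rate is shifted separately by arm. Do not adjust the primary contrast for survey mode: it arises after randomisation and is tied to app engagement, so adjusting for it can introduce bias.

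The cost is a little more analysis work and slightly wider intervals. No extra data and no change of design are needed.
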